**Fig. 2 Fig2:**
[figure not shown]
**a** Patient-controlled inhalation of premixed analgesic gas during exercise. **b** Patient’s pain was evaluated with a Numerical Rating Scale (NRS) during exercise, blood pressure was also measured. **c** Active range of motion was measured by goniometer and oxygen saturation of blood was monitored after exercise

### Measures

The following parameters will be recorded by the performer: age, sex, baseline pain score, blood pressure, heart rate, and oxygen saturation of blood monitored using Infinity Delta XL (Draeger Medial Systems Inc., Danvers, Shanghai, China) [25]. During mixture inhalation, pulse oximetry monitoring will not be necessary because the patients breathe 50% oxygen resulting in hyperoxemia, and the diffusion hypoxia phenomenon does not appear in this type of nitrous oxide use. For safety, we will measure oxygen saturation. Patients will rate their knee pain on the operated side with a numerical rating scale with endpoints of 0 (no pain) and 10 (worst pain tolerable) during flexing [23]. Pain severity, blood pressure, heart rate and oxygen saturation of blood will be monitored immediately after functional exercise begins (T0), 5 min (T1) after the beginning of functional exercise, and 5 min (T2) after functional exercise finishes. Both patients’ and therapists’ satisfaction with pain control under the new analgesia will be investigated by a 5-point satisfaction scale (5, very satisfied; 4, satisfied; 3, uncertain; 2, dissatisfied; 1, very dissatisfied). The KSS [11] will be obtained by questionnaire. According to our previous qualitative study, one of the substantial indicators of discharging from hospital for TKA patients is knee range of motion (ROM) ≥ 90°. Thus, the postoperative knee ROM will be measured by goniometer, and the time to reach ROM ≥ 90° will also be recorded. Moreover, adverse effects, and rescue analgesic need should be recorded and compared.

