Orally administered analgesics are often the main treatment in the immediate- to short-term postoperative period. Despite the effectiveness of opioids, they often lead to some undesirable side effects such as vomiting, constipation, and respiratory depression [10]. It is reported that continuous femoral nerve block (CFNB) with local anesthetics could provide superior analgesia and fewer side effects compared with systemic opioids, thus promoting exercises to increase the knee’s range of motion. Nevertheless, a drawback of CFNB is that it can cause a temporary, reversible weakness that accentuates that already caused by TKA and a subsequent increased risk of falling, thus delaying the ability to move [10, 11]. Nitrous oxide, which has been known as an analgesic gas for more than two centuries, is an effective, fast, safe, and noninvasive form of pain relief in the rehabilitation of patients. Different trials have confirmed that the use of nitrous oxide/oxygen can lead to obvious pain relief in different areas of medicine such as labor, colonoscopy, percutaneous liver biopsy, transrectal biopsy of the prostatic gland, migraine, skin laceration repair, venous cannulation, and dentistry [12–18]. The working mechanism of nitrous oxide/oxygen reported by Emmanouil et al. and Carbajal et al. [19, 20] is that it can stimulate neuronal release of endogenous opioid peptides and activate opioid receptors, aminobutyric acid type A (GABA), and noradrenergic pathways. The anxiolytic and sedative effects resemble those of benzodiazepines. Nitrous oxide hardly dissolves in blood and cannot bind to hemoglobin, acts swiftly and is metabolized by the lungs after inhalation ceases [21]. In 1961, Tunstall developed a stable mixture of nitrous oxide and oxygen for pain relief during childbirth. The two gases were mixed in equal proportions and stored in a single cylinder [22]. Soon, the analgesic use of this gas mixture spread over other settings, such as the dental office, prehospital emergencies, etc. In France, the gas mixture was used only in prehospital care and in some labor rooms, and later in procedure-related pain for children [23]. The mixture could play the same role as at least a 15-mg dose of morphine given intramuscularly [16]. It has been observed that all side effects (nausea, vomiting, dizziness) were transient and vanished within 5 min after removing the inhalation device. No serious side effects were noted [23]. However, this new kind of analgesic has not been accepted all over the world. It is mainly used in developed regions including Britain, Australia, and South Africa. In China, it was firstly used in obstetrics, and later in burns surgery [24]. The apparatus is cheap and portable, but most important is that it is easy for patients to control the device. However, its use in TKA postoperative exercise pain control is rarely reported. This study postulates that a nitrous oxide/oxygen mixture can alleviate the pain level to a certain degree, though not absolutely eliminate the pain of rehabilitative exercise.

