### Randomization and blinding

According to the computer-generated random number table in a 1:1 ratio, all the participants will be randomized to the intervention group (conventional treatment plus nitrous oxide/oxygen) or the control group (conventional treatment plus oxygen). The allocation sequence of each patient will be decided by a computer-generated schedule, which will be numbered by a statistician. The randomization schedule will be kept and sealed in an independent research room. Apart from the project manager, who is responsible for gas distribution, no other nurses or data collectors will have access to the data allocation. Prior to, and during, the treatment period, the participants, therapists, and the investigators will all be blind to the allocation. Only the project manager will know the allocation. The two gases will be stored in identical-looking canisters labeled A and B (Additional file 2). Patients given the letter A will be treated using a canister with the appropriate letter containing premixed nitrous oxide/oxygen. Those with letter B will be given oxygen only.

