### Procedure

All the procedures will be carried out in the rehabilitation department. All the patients will be recruited on the basis of being without any other analgesic before this study. The patients will inhale the premixed nitrous oxide/oxygen or placebo gas through a close-fitting mask for 2 min before exercise and throughout the whole process. They will be continuously monitored with a pulse oximeter during the whole process, and blood pressure will be taken before, during and after each functional exercise session. The inhaled mixture will be administered by the patients themselves (Fig. 2). Neither the therapists nor the patients know which gas mixture will be contained in each gas holder. During the functional exercise, the patients will inhale the gas mixture continuously. The inhalation of the gas mixture will be stopped when the functional exercise ends.

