#### Secondary outcomes

Secondary outcomes will include physiological parameters: blood pressure, heart rate, oxygen saturation at T0, T1, and T2, adverse effects, and satisfaction investigated by a 5-point satisfaction scale (5, very satisfied; 4, satisfied; 3, uncertain; 2, dissatisfied; 1, very dissatisfied) from both patients and therapists, KSS, and the time for ROM ≥ 90°(ROM will be measured by a goniometer). Rescue analgesia should also be an indicator and recorded.

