#### Adverse effects and emergency measures

Respiratory adverse effects, such as desaturation (pulse oximetric saturation≦ 94%), arterial hypotension or bradycardia—as well as hallucination and gastrointestinal adverse effects (nausea, vomiting) or any other discomfort—will be evaluated and recorded during and after the procedure. If any of these happen, patients will be given oxygen inhalation, and the discomfort should vanish within 5 min.

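### Oxygen saturation at T0 and T1 is read on oxygen-enriched gas in both arms, so that between-arm comparison says very little about ventilation

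*Protocol article*

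**What the plan says.** **Exposure.** Under Procedure, patients inhale their assigned gas "for 2 min before exercise and throughout the whole process", and "The inhalation of the gas mixture will be stopped when the functional exercise ends". Arm A receives nitrous oxide and oxygen 1:1. For arm B, Randomization and blinding states: "Those with letter B will be given oxygen only".

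**Timing.** Measures places T0 at the start of exercise and the other readings at "5 min (T1) after the beginning of functional exercise, and 5 min (T2) after functional exercise finishes".

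**Outcome.** Secondary outcomes lists "blood pressure, heart rate, oxygen saturation at T0, T1, and T2".

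**Event definition.** Adverse effects and emergency measures gives this example: "Respiratory adverse effects, such as desaturation (pulse oximetric saturation≦ 94" per cent. Recording covers the time during and after the procedure, and patients with any listed effect are given oxygen.

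**Monitoring.** Procedure calls for continuous pulse oximetry throughout. Measures says oximetry is unnecessary during inhalation, because "the patients breathe 50% oxygen resulting in hyperoxemia", and then says saturation will be measured for safety.

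**The concern.** Saturation cannot exceed 100%. When inspired oxygen is high, arterial oxygen tension lies on the flat part of the dissociation curve, and a large fall in ventilation barely moves SpO2. Two of the three scheduled readings are taken under that condition in both arms. The article itself gives this as the reason why oximetry on the mixture is unnecessary, yet it makes the same readings a trial outcome.

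At stake is what the trial can conclude about respiratory safety. A finding of no difference at T0 and T1 is close to guaranteed whatever the mixture does to breathing, and could be read as evidence of no respiratory effect. The article raises enrolment from a calculated 14 to 140 partly on safety grounds and foresees wide use if the treatment succeeds, so that reading would matter.

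**Working it through.** The article gives no SpO2 figure to reproduce. The check has two parts.

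**1. Which readings are on gas?**

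| Reading | Time | Gas status |
|---|---|---|
| T0 | start of exercise | on gas, about 2 min in |
| T1 | 5 min after start | on gas, if exercise lasts at least 5 min (duration not stated) |
| T2 | 5 min after the end | off gas for 5 min |

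No reading is scheduled between mask removal and T2.

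**2. How far would ventilation have to fall before SpO2 showed it?**

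Input from the article: inspired oxygen fraction (FiO2) 0.50 in arm A. Assumptions not in the article: barometric pressure PB 670 to 760 mmHg, alveolar-arterial gradient 15 to 60 mmHg, respiratory quotient 0.8, steady state, no mask leak.

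- PaO2 = FiO2 × (PB − 47) − PaCO2/0.8 − gradient
- SpO2 = 100 / (1 + 23400/(PaO2³ + 150 × PaO2))

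The second formula gives 94% at PaO2 = 70.9 mmHg. Hence PaCO2 at 94% = 0.8 × (FiO2 × (PB − 47) − 70.9 − gradient).

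On 50% oxygen, FiO2 × (PB − 47) is 0.5 × 713 = 356.5 mmHg, or 0.5 × 623 = 311.5 mmHg:

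| PB, gradient | PaO2 at PaCO2 40 | SpO2 | PaO2 at PaCO2 80 | SpO2 | PaCO2 at 94% |
|---|---|---|---|---|---|
| 760, 15 | 291.5 | 99.9% | 241.5 | 99.8% | 216.5 |
| 760, 60 | 246.5 | 99.8% | 196.5 | 99.7% | 180.5 |
| 670, 15 | 246.5 | 99.8% | 196.5 | 99.7% | 180.5 |
| 670, 60 | 201.5 | 99.7% | 151.5 | 99.3% | 144.5 |

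Doubling PaCO2 from 40 to 80 mmHg lowers predicted SpO2 by at most about 0.4 percentage points (99.7% to 99.3%). Reaching 94% by hypoventilation alone would need PaCO2 of about 145 to 217 mmHg.

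A second calculation used the full alveolar gas equation and an arterial/alveolar ratio of 0.75 to 1.0 in place of a fixed gradient. On 50% oxygen it gave 99.3 to 99.9% over PaCO2 40 to 100 mmHg, and about 190 to 230 mmHg to reach 94% (ratio 0.75). For arm B, whose delivered oxygen fraction is not stated, an assumed FiO2 of 0.7 to 1.0 gave 99.8 to 100%.

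**Room air, for the off-gas readings.** At 760 mmHg and gradient 15, 94% is reached at PaCO2 = 0.8 × (0.21 × 713 − 70.9 − 15) = 51 mmHg. At 670 mmHg and the same gradient it is reached at 0.8 × (0.21 × 623 − 70.9 − 15) = 36 mmHg, below a normal 40. There, PaO2 at PaCO2 40 is 130.8 − 50 − 15 = 65.8 mmHg, an SpO2 of about 92.7%. Off-gas SpO2 can therefore respond to ventilation, but a fixed 94% limit may be met at normal ventilation if barometric pressure is low.

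**The case against.** The strongest reply is that the protocol does not depend on T0 and T1 alone. Oximetry is continuous under Procedure, adverse effects are recorded after as well as during the procedure, and T2 is off gas. Desaturation is only an example, and any other discomfort is also recorded. The article acknowledges hyperoxemia and states no SpO2 hypothesis and no planned claim of respiratory safety.

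Much of this stands, and it rules out stronger readings that a reader might infer:

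- **That the 94% rule cannot detect a respiratory effect.** The documents do not support this. The rule also applies off gas. The calculation models steady hypoventilation only, and apnoea, obstruction or mask removal could still show on continuous oximetry.
- **That T2 is empty because side effects have gone by then.** The Background does say that side effects "were transient and vanished within 5 min after removing the inhalation device", but the effects it lists there are nausea, vomiting and dizziness, none of them respiratory, and the statement reports a cited source. T2 is a thin check, not a void one.
- **That 51 mmHg is a general room-air contrast.** It holds only at the most favourable corner of the assumed range.
- **That oxygen is the wrong comparator.** It is the declared placebo, and this point is no objection to it.

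The reply does not make SpO2 at T0 and T1 informative about ventilation. Those readings are named as outcomes, and the interval just after mask removal has no scheduled value. The article asserts that diffusion hypoxia does not appear with this use; a reading in that interval would let the trial check the assertion.

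**Conclusion.** The point holds in limited form. SpO2 at T0 and T1 is near its ceiling in both arms: about 99% or higher on 50% oxygen even at a PaCO2 of 80 mmHg. As a between-arm outcome it says very little about ventilation, and the 94% criterion is very insensitive to hypoventilation while gas is inhaled. Only off-gas readings can inform that question, and the schedule has one, 5 min after the gas stops.

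The figures rest on assumed physiology, but the on-gas conclusion is the same across the whole assumed range and under both calculations. The ceiling in arm B is an inference from the words oxygen only, though a safe one. The T1 part needs exercise to last at least 5 min. This affects what can be concluded about respiratory safety; it does not touch the primary pain outcome.

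**What to change.** - Record an explicit pre-gas SpO2 on room air, before the 2 min of inhalation. Measures lists oxygen saturation among the recorded parameters but does not clearly time a pre-gas value.
- Define the SpO2 safety outcome as the lowest reading between mask removal and T2, from the oximeter already fitted, as change from the pre-gas value. Using change matters because room-air SpO2 may already be near 94% at lower barometric pressure.
- Flag any reading taken while oxygen was being given for an adverse effect.
- Tabulate events at or below 94% on gas and off gas separately.
- Report SpO2 at T0 and T1 descriptively. State that inspired oxygen was high and differed between arms, and that these values do not support a claim of no respiratory effect.
- Reconcile Procedure (continuous oximetry) with Measures (oximetry unnecessary during inhalation).

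Cost: two extra recorded values per session, the oximeter left on until T2, and a wording change to one secondary outcome. The on-gas comparison loses its standing as a safety result.

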### Outcome measures

#### Primary outcome

The primary endpoint measures will be pain severity at T0, T1, and T2. The anticipated pain score (Numerical Rating Scale; NRS) during functional exercise will be a reduction from to 3 to 5 in the intervention group. Repeated-measures analysis of variance will be used for data analysis.

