**Methods/design:**

This double-blind, randomized, placebo-controlled study will be implemented in the Rehabilitation Department in the General Hospital of Ningxia Medical University. Patients aged between 50 and 75 years who underwent a primary unilateral total knee arthroplasty are eligible for inclusion. The key exclusion criteria include: epilepsy, pulmonary embolism, intestinal obstruction, aerothorax. The treatment group (A) will receive a pre-prepared nitrous oxide/oxygen mixture plus conventional treatment (no analgesics), and the control group (B) will receive oxygen plus conventional treatment (no analgesics). Patients, physicians, therapists, and data collectors are all blind to the experiment. Assessments will be taken immediately after functional exercise begins (T0), 5 min (T1) after functional exercise begins, and 5 min after functional exercise has finished (T2). Patients will be randomly allocated between a treatment group (A) and a control group (B) in a ratio of 1:1. Primary outcome, including pain severity in the procedure, will be taken for each group. Secondary outcomes include blood pressure, heart rate, oxygen saturation, side effects, knee joint range of motion, Knee Society Score (KSS), rescue analgesia need, and satisfaction from both therapists and patients.

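### The primary endpoint pools T0, T1 and an off-gas, post-exercise T2 in one repeated-measures ANOVA, and the plan does not say which test decides

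*Protocol article*

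**What the plan says.** All references are to the protocol article.

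- **Endpoint and method (Primary outcome):** "The primary endpoint measures will be pain severity at T0, T1, and T2", and then "Repeated-measures analysis of variance will be used for data analysis". No time point, model term or contrast is singled out. The same section states the expected benefit for pain during the exercise. Data analysis adds only a 0.05 significance threshold.
- **Timing (Measures):** scores are taken "immediately after functional exercise begins (T0), 5 min (T1) after the beginning of functional exercise, and 5 min (T2) after functional exercise finishes".
- **Scale (Measures):** the NRS runs between "0 (no pain) and 10 (worst pain tolerable) during flexing".
- **Gas (Procedure):** patients inhale "through a close-fitting mask for 2 min before exercise and throughout the whole process", and "The inhalation of the gas mixture will be stopped when the functional exercise ends".
- **Abstract:** "Primary outcome, including pain severity in the procedure, will be taken for each group".
- **Sizing (Sample size determination):** success is a 30% fall in pain between T0 and T1. T2 plays no part.

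**The concern.** The trial asks whether the gas reduces pain while patients exercise. At T2 the exercise has been over for 5 minutes and so has the inhalation. The knee is no longer being worked, which fits poorly with a scale anchored to flexing. Even so, T2 has the same primary status as the two on-treatment readings.

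A two-arm, three-time repeated-measures ANOVA also gives two tests that bear on treatment, and they ask different things. The group effect asks whether the average over the three times differs between arms. The group-by-time term asks whether the difference between arms changes over time. The two can disagree on the same data, and the plan does not say which one counts. At stake are the size of the reported effect, what it means, and the false-positive rate of the primary claim.

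**Working it through.** **1. The plan's own figure.** Sample size determination gives 7 per group for 80% against 20% responders at two-sided 0.05. Power is not stated. With 80% power assumed and unpooled variance:

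n = (1.960 + 0.842)² × (0.8×0.2 + 0.2×0.8) / (0.8 − 0.2)² = 7.85 × 0.32 / 0.36 = 6.98, so 7 per group.

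The figure reproduces, but for a responder comparison built on T0 and T1. It says nothing about a three-time ANOVA. The planned total is 140, or 70 per arm at 1:1.

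**2. Status of each reading**

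| Reading | Exercise | Gas |
|---|---|---|
| T0 | just begun | on, after 2 min of inhalation |
| T1 | 5 min in | on |
| T2 | ended 5 min earlier | off since exercise ended |

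**3. Dilution of the group effect.** It averages the three differences equally. No SD is needed.

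- Effect d at T0 and T1, none at T2: (d + d + 0)/3 = 0.67d
- Half at T0, full at T1, none at T2: (0.5d + d + 0)/3 = 0.50d
- T1 only: (0 + d + 0)/3 = 0.33d

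**4. Power.** Assumed, not in the document: SD 2 NRS points, correlation 0.5 between times, and the effect patterns. From the document: 70 per arm.

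- SD of a patient's three-time mean: 2 × √((1 + 2×0.5)/3) = 1.633
- SE of the group effect: 1.633 × √(2/70) = 0.276
- SE of the T1 difference: 2 × √(2/70) = 0.338

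Power for the group effect and for T1 comes from the t-test with 138 degrees of freedom and noncentrality (effect/SE). For example, 0.667/0.276 = 2.42 and 1/0.338 = 2.96. For group-by-time, the F-test has 2 and 276 degrees of freedom and noncentrality 35 × Σ(dₜ − d̄)² / (4 × 0.5).

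| Effects at T0/T1/T2 | Group effect | Group-by-time | T1 alone |
|---|---|---|---|
| 1/1/0 | 67% | 87% | 84% |
| 0.5/1/0 | 44% | 75% | 84% |
| 0/1/0 | 22% | 87% | 84% |
| 1/1/1 | 95% | 5% | 84% |
| 2/2/0 | over 99% | over 99% | over 99% |
| 1/2/0 | 95% | over 99% | over 99% |
| 0/2/0 | 67% | over 99% | over 99% |

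Simulation of the full ANOVA agrees to within about two percentage points.

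**5. False positives.** If a significant result on either F-test may be called success, and the two are treated as independent, the risk is 1 − 0.95² = 9.75%. Simulation under no effect, with correlations 0.3 to 0.7, gave 9.5% to 9.9%.

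**The case against.** The case for the plan has several strong parts.

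- **Dilution is not a property of the whole ANOVA.** Only the group effect is diluted. In the 1/1/0 pattern the group-by-time term (87%) slightly beats T1 alone (84%). This stands, but it also shows that the answer depends on a choice the plan leaves open.
- **A 1-point effect is small for this trial.** The sentence on the anticipated score is garbled, but it reads either as a fall from 5 to 3 or as a fall of 3 to 5 points, so at least 2 points. At 2 points the group effect keeps 95% power or more unless the effect is confined to T1. That last case is doubtful, since patients have already inhaled for 2 minutes before T0. This stands, and power is not the main harm.
- **The deciding term can be left to a statistical analysis plan.** This is partly right. But the article itself fixes three joint primary times, one of them off treatment, and a later analysis plan would inherit that.

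A reader might infer three stronger points that the document does not support.

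- **That analgesia is stated to be gone by T2.** The Background sentence saying that effects "were transient and vanished within 5 min after removing the inhalation device" is about nausea, vomiting and dizziness. Little effect at T2 is only an inference, from the Background's account of fast action and of clearance through the lungs once inhalation stops. No time to loss of analgesia is given.
- **That a win at any one of the three times would count.** That rule would carry an 11% to 14% error rate, but the plan states no such rule. It plans one ANOVA.
- **That patients with a missing score will be lost.** Standard repeated-measures ANOVA does drop them, but the document gives no rate of missing scores and T1 comes only 5 minutes into exercise. The point is speculative.

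**Conclusion.** The concern holds in a limited form. The protocol text makes an off-gas, post-exercise reading jointly primary with two on-treatment readings, against its own description of the outcome as pain during exercise and a sizing criterion that ignores T2. It leaves the deciding test open.

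The dilution to 0.67d or 0.33d is pure arithmetic once T2 is taken to carry no effect. That premise is inferred, and any residual effect at T2 would lessen the dilution. The near-zero power of the group-by-time term for a constant effect, and the error rate of about 10% if either test may count, do not depend on that premise. The power figures rest on the assumed SD, correlation and effect patterns. They show a material loss at 1 point and mostly a small one at 2.

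The trial is not shown to be underpowered. The main harm is an estimate that is smaller and harder to interpret, and a primary test that could be chosen after the data are seen.

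**What to change.** 1. Make the between-arm difference in NRS at T1 the single primary test, at two-sided 0.05. Do not use T1 minus T0: T0 follows 2 minutes of gas, so an effect already present and equal at both times cancels out (about 5% power).
2. Adjust for the baseline pain score listed under Measures if it is taken before any gas. The article does not give its timing, so state it.
3. Make T0 and T2 secondary, and state what the NRS refers to at T2, when the knee is not being exercised.
4. If all three times are modelled, use a linear mixed model with treatment-by-time and name the T1 contrast as the primary test.
5. Align the success definition under Sample size determination with this test.

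The cost is a change of wording before unblinding. The same data are collected and no further patients or visits are needed. The one downside is that T0 and T2 lose primary status. Because T0 is also on gas and during exercise, demoting it is a design choice. T1 is preferred because it is taken furthest into the exercise while the gas is on.
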